### Proposed primary and secondary outcome measures

The primary outcome will be the rate of hospital days per 1,000 disease episodes. If differences in rate of hospital days between intervention groups are detected, we will explore to what degree they are due to a change in rates of admission versus a change in hospital lengths of stay.

The secondary outcomes will be utilization of appropriate therapies including:

▪ Proportion of patients treated in the emergency department and hospital with a corticosteroid.

▪ Proportion of patients evaluated in emergency department for at least three hours after treatment with corticosteroids before the decision to admit to hospital is made.

▪ Time to treatment with corticosteroids in both emergency department and hospital patients.

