#### Variability in treatment practices

A recent study reported significant differences in the proportion of children treated with mist, epinephrine, and salbutamol based on whether physicians were pediatricians or not.[50] All physicians in these two urban hospitals, however, used corticosteroids in more than 90% of children with croup. In contrast, our data from Alberta shows that a much smaller proportion of children receive corticosteroids, (e.g. only 22% at the 12 smaller hospitals). In these same small hospitals, the same proportion of children receive antibiotics or salbutamol; treatments for which there is no evidence of efficacy.

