#### Secondary objective

To determine which of the three intervention strategies are most effective at increasing the use of therapies of known benefit.

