## Methods

### Proposed trial design

We will conduct a cluster randomized controlled trial after completing a baseline survey. In order to provide a comprehensive answer as to whether or not our interventions are beneficial, we have obtained data from several different sources. The stages are as follows.

1. Baseline survey (currently near completion):

▪ Utilizing administrative data, we have documented Alberta health care utilization rates.

▪ We are documenting severe adverse outcomes in Alberta utilizing administrative data, and both medical examiner and records audit.

▪ Using this data, we have rank ordered Alberta hospitals based on number of disease episodes and rates of hospitalization.

▪ We have enrolled the highest ranking 24 hospitals who consented to participation.

▪ We are documenting practice patterns in these 24 selected Alberta hospitals utilizing medical records audit.

▪ Utilizing a prospective cohort questionnaire, we are documenting the duration of clinical symptoms of children with croup and the psychosocial burden on their families in the same 24 selected Alberta hospital emergency departments

2. Development of clinical guidelines that address indications for drug therapy and hospital admission/discharge criteria. The process will include:

▪ convening an guideline committee with a range of disciplines and professions;

▪ critically reviewing the published literature;

▪ drafting guidelines which meet standard criteria for developing guidelines;

▪ review of the guidelines by both parents and a wide-range of users (family physicians, nurses, and respiratory therapists);

▪ obtaining approval of the guidelines from the Canadian Pediatric Society, Canadian Association of Emergency Physicians, and the Alberta Medical Association; and

▪ publishing the guidelines in journals such as the Canadian Medical Association Journal.

3. Randomization of 24 Alberta hospitals to one of three implementation strategies.

4. A follow-up survey whose purpose is to detect any change from baseline by:

▪ documenting severe adverse outcomes and utilization rates in Alberta;

▪ documenting practice patterns in the 24 Alberta hospitals surveyed at baseline;

▪ documenting the duration of symptoms of children with croup and the psychosocial burden on their families attending these 24 hospital emergency departments.

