### Proposed analyses

The principal analysis will examine hospital stays arising from individual disease episodes over the six-year baseline and study period. We will apply a linear mixed model (Laird-Ware approach) incorporating random effects for hospital, year within hospital, as well as fixed effects for intervention and year. We will also pursue a more detailed explanatory analysis incorporating individual subject characteristics (age, sex) as well as random effects for admission and discharge physician. Additionally we will develop similar models for length of stay restricting to disease episodes leading to admissions, and mixed effects logistic regression model for admissions. Secondary analyses relating to steroid use and *Telephone OutPatient (TOP) *scores will follow a similar format. The examination of day 1- 3 *TOP *scores will require augmenting the basic model framework to include random subject effects and a serially correlated (within subject) residual error structure. No subgroup analyses are planned.

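### Time to corticosteroid has a value only in treated children, a group the interventions aim to enlarge, so a treated-only comparison between arms is confounded by case mix

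*Protocol article*

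**What the plan says.** The section on primary and secondary outcome measures lists three secondary outcomes:

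- "Proportion of patients treated in the emergency department and hospital with a corticosteroid". Every audited child can be scored on this.
- "Proportion of patients evaluated in emergency department for at least three hours after treatment with corticosteroids before the decision to admit to hospital is made". No denominator is given.
- "Time to treatment with corticosteroids in both emergency department and hospital patients". No rule is given for a child who is never treated.

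Under Proposed analyses, the principal model is a linear mixed model with random effects for hospital and year within hospital, and fixed effects for intervention and year. A mixed logistic model is named for admissions. Then, "Secondary analyses relating to steroid use and" TOP scores are to be built along the same lines. That section mentions neither censoring nor competing events. Age and sex are the only child characteristics named, and they belong to an explanatory analysis.

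The Secondary objective is "To determine which of the three intervention strategies are most effective at increasing the use of therapies of known benefit". The trial design section lists "Development of clinical guidelines that address indications for drug therapy and hospital admission/discharge criteria". Baseline steroid use is reported as "only 22% at the 12 smaller hospitals".

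**The concern.** Whether a child has a time to treatment depends on a decision made after randomisation, and changing that decision is what the interventions are for. If a strategy brings steroids to children who would otherwise have gone without, those children enter the average in that arm only. The arms then differ in who is being averaged as well as in how quickly they are treated. Random hospital effects and the baseline years do not remove this, because the change in case mix happens within hospitals and is caused by the intervention.

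At stake is the reading of a named secondary outcome. A strategy that treats every child as fast or faster could show a longer mean time, or a strategy with no effect on speed could seem to shorten it.

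The three-hour outcome is exposed in the same way if it is scored among treated children with an admission decision, since both conditions are targets of the guideline.

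**Working it through.** The plan gives no sample size or power for these outcomes, so there is no figure to reproduce. The check is of who contributes, followed by illustrations. Apart from the 22%, the minutes, severity shares and admission shares below are assumptions.

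**1. Who has a value.** At 22% use, 22 of 100 children have a time and 100 − 22 = 78 have none. At an assumed 80% use, 20 have none. The 22% applies to the 12 smaller hospitals, not to a whole arm.

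**2. Effect of changing the mix alone.** Assume 15% of children are severe. Severe children are treated at 30 min and mild children at 90 min at every level of use, so nobody is treated later anywhere. The share of severe children treated is 60%, 80% and 95% as overall use is 22%, 50% and 80%. Mean among treated = (severe treated × 30 + mild treated × 90) / all treated, per 100 children:

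| Overall use | Severe treated | Mild treated | Severe share of treated | Mean among treated |
|---|---|---|---|---|
| 22% | 15 × 0.60 = 9 | 13 | 41% | (270 + 1170)/22 = 65 min |
| 50% | 15 × 0.80 = 12 | 38 | 24% | (360 + 3420)/50 = 76 min |
| 80% | 15 × 0.95 = 14.25 | 65.75 | 18% | (427.5 + 5917.5)/80 = 79 min |

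The apparent delay is 79.3 − 65.5 = about 14 min, with no true delay in either group.

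**3. Range and direction.** With 10% to 30% severe and times of 30/60, 30/90 or 45/60 min, the shift from 22% to 80% use runs from 58.2 − 55.9 = 2.3 min to 68.6 − 40.9 = 27.7 min. If the times in step 2 are exchanged (severe 90, mild 30), the means are (810 + 390)/22 = 54.5 and (1282.5 + 1972.5)/80 = 40.7 min, an apparent gain of about 14 min. If both groups are treated equally fast, there is no shift.

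**4. The same children with everyone in the denominator.** On the step 2 inputs, any cut-off between 30 and 90 min counts only severe treated children: 9, 12 and 14.25 per 100. Any cut-off above 90 min counts all treated children: 22, 50 and 80 per 100. Neither series worsens.

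**5. Three-hour outcome, if restricted to admitted children.** Per 1,000 emergency children, assume 150 severe with 40% admitted (60), and 850 mild with 10%, 5% or 2% admitted (85, 42.5, 17). Keep the chance of a completed wait fixed at 0.2 (severe) and 0.6 (mild):

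- (12 + 51)/145 = 43%
- (12 + 25.5)/102.5 = 37%
- (12 + 10.2)/77 = 29%

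With the two chances swapped, the results are 53/145 = 37%, 44.5/102.5 = 43% and 39.4/77 = 51%. The proportion moves either way with no change in behaviour within a group.

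**6. Audit sampling.** The section on practice patterns reviews all hospitalized children, but caps emergency records at 30 per year at baseline and 100 at follow-up. For a hospital with A admitted children a year and both caps reached, admitted children make up A/(A + 30) of an unweighted pool at baseline and A/(A + 100) at follow-up. For an assumed A of 10 that is 25% and then 9%; for A of 30, 50% and then 23%. Pooling all audited children without weights would therefore add a shift between periods.

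**The case against.** The strongest reply is that the defect is inferred. The outcome wording does not restrict either measure to treated or admitted children. The analysis section names steroid use but not time to treatment. A similar format may mean only the same clustering and year structure, and the handling of untreated children could be settled in an analysis plan. Part of this stands: the denominator of the three-hour outcome is not stated, and if it is all emergency children the selection disappears. A low value would then mix children untreated, not admitted and admitted early. It stands less well for time to treatment. The models named are linear and logistic, neither can carry a time for an untreated child, and no time-to-event approach is indicated.

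A second reply is that the real changes show up elsewhere. This is right. More treatment appears in the proportion treated, and fewer admissions in the primary outcome and the admissions model. A reader might infer that a flat three-hour proportion would conceal a large fall in admissions; those other analyses would reveal it. What could be lost is narrower: the split of admissions into early and later.

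A reader might also infer that effective strategies will look slower because newly treated children are milder and treated later. The documents say nothing about their severity or timing, and steps 3 and 5 show that the sign depends on the assumption.

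Finally, a conditional measure is a fair adherence question. It is, as description, but not as the randomised comparison.

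**Conclusion.** The point holds for time to corticosteroid: as worded, and in the model format given, it compares arms on treated children only, while the treated group is meant to differ by arm. For the three-hour outcome it holds conditionally, on the reading that the denominator is treated children with an admission decision.

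The bias is of unknown size and direction. The 2 to 28 minute range is an illustration. It needs three things: untreated children left out, use that differs between arms, and timing that differs by kind of child. The second is the trial's own hope; the third is an assumption.

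The documents do not support a claim that both outcomes are defined only in selected children, nor that the trial's main result is at risk. The primary outcome uses all disease episodes. The change is worth making because it is cheap and concerns a named secondary outcome, and possibly two of the three.

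**What to change.** - **Time to steroid.** Analyse it in all audited croup children as the proportion given a steroid within a pre-set time of arrival, using a mixed logistic model with hospital as the cluster. Untreated children count as not treated within that time. Where departure times are available, cumulative incidence with leaving untreated as a competing event is an alternative.
- **Sampling.** Analyse emergency and hospitalized samples separately, or weight each record by its sampling fraction. Each hospital already lists all its croup records, so the fractions can be obtained.
- **Three-hour outcome.** State the denominator. Add a version in all emergency children: the proportion admitted without a completed three-hour wait after steroid.
- **Keep as description.** Report the treated-only mean time and the conditional three-hour proportion as adherence measures, not as the comparison between arms.

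The cost is revised outcome wording, weighting, and some extra chart times. Arrival times are needed for the main version and departure times only for cumulative incidence. The baseline audit is nearly finished, so it should be checked now which times were recorded. The result will no longer be a simple mean time.

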#### Other outcomes

##### Clinical outcomes

To determine which dissemination strategy will most effectively maintain or improve clinical outcomes:

▪ by reducing or maintaining the number of uncommon, severe clinical events such as intubation, respiratory and cardiac arrest, anoxic brain injury, or death.

▪ by reducing, (in a prospective cohort of children enrolled from each hospital) croup symptoms on days 1, 2, and 3 following assessment, as measured by a telephone follow-up

▪ assessment tool (Telephone Out Patient (TOP) score).

##### Psychosocial burden

To determine which dissemination strategy will most effectively maintain or reduce the psychosocial burden on parents by

▪ reducing, (in a cohort of children enrolled from each hospital), the stress experienced by the primary caregiver due to the child's illness on days 1–3 following assessment.

▪ reducing, (in a prospective cohort of children enrolled from each hospital), the number of hours of sleep missed by the child due to croup on days 1–3 following assessment.

### How will the outcome measures be measured at follow up?

#### Utilization outcomes

Previously discussed.

#### Adverse outcomes

Previously discussed in part.

##### Development of data abstraction sheet

The Principal Investigator and Study Coordinator, following an informal review of medical records, developed a customized Access relational database. This draft database was pilot tested and revised before beginning formal review.

##### Auditing process

Because these cases are significantly more complex, only the study coordinator and another trained senior pediatric emergency nurse will perform these audits. The principal investigator and the two nurses will meet regularly during the baseline and follow up audits, to discuss cases and any difficulties encountered in auditing. To establish the degree of agreement between auditors, the three will review a random selection of medical records.

##### Case identification: multiple and overlapping methods

In order to minimize the likelihood that any adverse outcomes will be missed, overlapping methods for identifying cases will be used. Specifically, we will obtain provincial medical examiner records, and hospital administrative data from the province, all the health regions, and all the hospitals in urban areas.

#### Practice pattern outcomes

##### Development of data abstraction sheet

After an informal review of medical records, a customized Access relational database was developed. This draft data sheet was piloted and revised, before beginning formal review.

##### Training & monitoring of medical record auditors

The projector coordinator has trained two research assistants to review medical records and directly enter data in a relational database (Access). The project coordinator and each of the research assistants will review a randomly selected number of records through the study to check accuracy in data abstraction.

##### Accuracy of ICD9 coding

To assess the accuracy of using ICD9 coding to identify children diagnosed with croup, we will examine whether health record analysts coded records in the same way at each of the 24 hospitals. We will determine what percentage of children were coded as croup using the standard codes met a formal definition for croup (acute onset of stridor associated with a "seal-like" barking cough). Also to explore whether some hospitals use other ICD9 codes for children with croup, we will generate a list of potential alternative codes. Using this list of potential alternative ICD9 codes, we will review a random selection of medical records using these codes.

#### Clinical & psychosocial burden outcomes

##### RMO database

We are maintaining a database of all children diagnosed as having croup whose parents refused, were missed, or are otherwise excluded. Demographics and disease characteristics of children and their families in this database will be compared to those families who are administered the survey to ascertain if the two populations are different.

##### Telephone interviewing techniques

Several procedures should enhance the reliability of telephone data collection. a) One study investigator will complete all telephone follow up for a given family. b) At the time of enrolment the primary caretaker of the child will be identified, and every effort will be made to conduct all follow-up calls with this person. c) The questions will have standardized responses. d)A standard audio recording of a child with croup will be played to the caregiver to aid them in identifying the easily recognizable and distinctive cough.

### Proposed analyses

The principal analysis will examine hospital stays arising from individual disease episodes over the six-year baseline and study period. We will apply a linear mixed model (Laird-Ware approach) incorporating random effects for hospital, year within hospital, as well as fixed effects for intervention and year. We will also pursue a more detailed explanatory analysis incorporating individual subject characteristics (age, sex) as well as random effects for admission and discharge physician. Additionally we will develop similar models for length of stay restricting to disease episodes leading to admissions, and mixed effects logistic regression model for admissions. Secondary analyses relating to steroid use and *Telephone OutPatient (TOP) *scores will follow a similar format. The examination of day 1- 3 *TOP *scores will require augmenting the basic model framework to include random subject effects and a serially correlated (within subject) residual error structure. No subgroup analyses are planned.

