### Proposed sample size

The twenty-four participating hospitals were initially selected by calculating anticipated hospital specific effect sizes based on assuming that the effect of intervention would be proportional to baseline admission rates taking into account hospital-specific frequencies of disease episodes. Hospitals are to be randomized to one of three intervention arms, eight hospitals per arm, after stratification on baseline frequency of disease episodes. The power of our study depends on the anticipated change in mean hospital days as shown in Figure 1, which provides power estimates plotted against percentage decrease based on examining hospital stays over the three baseline and three post-intervention years. (Appendix A – Details of calculations) A Bonferroni correction for the two comparisons of intermediate and high intensity intervention against low intensity intervention has been included. The estimated power (overall alpha = .05) to detect a 25% change is 0.80 for each comparison.

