### Duration of the baseline and follow-up periods

#### Utilization and adverse outcome data obtained from the administrative datasets

We have extracted data from administrative databases from April 1^st^, 1994 to March 31^st^, 2000, providing six years of data. In summer 2006, we will again extract data from administrative databases from April 1^st^, 2000 to March 31^st^, 2006. Extraction of data across these time periods will allow us to extend the baseline utilization rates from six to nine years. Most importantly, this will ensure no significant changes occur just prior to the study interventions. Extraction of data through March 31^st^, 2006 will provide utilization data for the intervention and two follow-up years.

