#### Calculation of societal costs

Total societal costs (the sum of payer and non-payer costs) for each hospital will be calculated for the 9 baseline years, the one-year of intervention, and the two years of follow-up. Given the year-to-year variability in the incidence of croup, the total societal costs for each year will be adjusted for disease incidence (total costs per year divided by the number of episodes of croup diagnosed that year by those physicians assigned to the hospital). An average cost per year for the baseline period will be calculated. Statistical assessment of whether or not costs differ between the three intervention groups will be calculated by the Laird-Ware model with baseline costs as the covariate. (This type of analysis will allow us to simultaneously compare costs at three time points (the intervention year and two years of follow-up), while adjusting for the baseline cost)

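### The primary model does not say whether intervention means allocated arm or a term that starts at roll-out; the first dilutes the effect, and the second needs an error term for lasting change within hospitals

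*Protocol article*

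**What the plan says.** Under Proposed analyses, the protocol article states: "The principal analysis will examine hospital stays arising from individual disease episodes over the six-year baseline and study period". The model is a linear mixed model "incorporating random effects for hospital, year within hospital, as well as fixed effects for intervention and year". No interaction of arm with period is listed, no baseline covariate is listed, and the coding of the intervention term over time is not given. Serial correlation appears only for the telephone scores, where the model is to "include random subject effects and a serially correlated (within subject) residual error structure". The steroid-use and telephone-score analyses are to take a similar form.

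The primary objective frames its null hypothesis as no reduction from baseline. For costs, the section Calculation of societal costs makes the baseline adjustment explicit: arm differences "will be calculated by the Laird-Ware model with baseline costs as the covariate".

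The number of baseline years differs between sections. Proposed sample size has power "based on examining hospital stays over the three baseline and three post-intervention years". Proposed analyses speaks of six years. The section on administrative data says that the second extraction "will allow us to extend the baseline utilization rates from six to nine years" and "will provide utilization data for the intervention and two follow-up years".

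**The concern.** A model that pools years before and after roll-out has to say which comparison carries the treatment effect. Main effects for intervention and year leave two readings, and each has its own weakness.

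If the term is the allocated arm, its coefficient is the average difference between arms over all years. Most or half of those years precede the intervention, and the coefficient also carries the standing differences between hospitals that the baseline data could have removed.

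If the term switches on at roll-out, the comparison is the right one. Its error term then comes from year-to-year scatter around each hospital's mean. A lasting change at one hospital between periods, for example through staff turnover or a local protocol, has no term of its own. With only eight hospitals per arm, the variation between hospitals in their change is what the test should be based on.

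At stake is either an estimate several times too small or a primary test with a type I error above its nominal level.

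**Working it through.** **Inputs.**
- 24 hospitals: "Hospitals are to be randomized to one of three intervention arms, eight hospitals per arm".
- Study years p = 3 (the intervention year and two follow-up years).
- Baseline years b = 3, 6 or 9, depending on the section.
- Effect 25%, power 0.80, overall alpha 0.05 with Bonferroni for two comparisons, so 0.025 each. Two-sided is my assumption.
- No variance component, intracluster correlation or between-year correlation is given.

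**Step 1, the stated power.** It cannot be reproduced without variance components; the appendix and the figure are not shown. It can only be inverted: 2.241 + 0.842 = 3.083, so the standard error is 25/3.083 = 8.11 percentage points. The implied SD of hospital-level change is 8.11/√(2/8) = 16.2 points.

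**Step 2, allocated-arm coding.** With years weighted equally and the full effect present in all study years, the expected coefficient is 25% × p/(b + p):
- 3+3: 25 × 3/6 = 12.5%
- 6+3: 25 × 3/9 = 8.3%
- 9+3: 25 × 3/12 = 6.3%

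If the standard error stayed at 8.11 points, power would be about 0.24, 0.11 and 0.07. In practice the standard error would differ, because this contrast includes variation between hospitals. With an assumed hospital SD of 1 and hospital-year SD of 0.3 (6+3 years), it is √[(2/8)(1 + 0.09/9)] = 0.50, against √[(2/8)(0.09)(1/6 + 1/3)] = 0.11 for the difference-in-differences.

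**Step 3, switch-on coding.** In simulation with those SDs, 6+3 years and a true effect of -0.40, the estimate averaged -0.404, with mean standard error 0.106 against an empirical SD of 0.109. So there is no dilution, and the standard error is right when hospital-years are independent given the hospital.

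Now let V be the covariance of one hospital's T = b + p yearly deviations, c the post-minus-pre contrast (-1/b and +1/p), and M the centring matrix.
- True variance of one hospital's change: c′Vc.
- Variance the model uses: s²·c′c, with s² = [23·tr(MV) − 2·c′Vc/c′c] / [23(T − 1) − 2].
- Ratio of model to true standard error: r = √(s²·c′c / c′Vc).
- Type I error: 2[1 − Φ(2.241·r)].

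Example: 6+3 years, yearly variance 1, and a hospital-specific shift between periods with variance 0.25.
- tr(MV) = 9.75 − 11.25/9 = 8.5; c′c = 1/6 + 1/3 = 0.5; c′Vc = 0.5 + 0.25 = 0.75.
- s² = (23 × 8.5 − 2 × 1.5)/182 = 192.5/182 = 1.058.
- r = √(1.058 × 0.5/0.75) = 0.840.
- Type I error = 2[1 − Φ(1.882)] = 6.0%.

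Type I error at nominal 2.5%:

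| Assumed extra correlation | 3+3 | 6+3 | 9+3 |
|---|---|---|---|
| None | 2.5% | 2.5% | 2.5% |
| Lag-1 correlation 0.3 | 6.4% | 7.1% | 7.1% |
| Lag-1 correlation 0.5 | 9.8% | 11.6% | 11.7% |
| Shift variance 0.25 of yearly | 4.8% | 6.0% | 6.7% |
| Shift variance 0.5 of yearly | 7.1% | 9.4% | 10.8% |

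A simulation of 24 hospitals in three arms (6,000 runs per setting) agreed: 4.8% to 12.0% with extra correlation and 2.1% to 2.8% without. An analysis of each hospital's change (21 df) stayed at 2.2% to 2.9% throughout. If each period has its own hospital effect with these variances, the rates are higher: 11.2% and 16.8% in a simulation with 9+3 years and 8 against 8 hospitals.

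**The case against.** The strongest reply is that the switch-on reading is the natural one. The objectives, the description of the follow-up survey and the power calculation all speak of change. On that reading, intervention plus year plus a random hospital effect is already a difference-in-differences: it needs no interaction, and the baseline years supply the adjustment. That stands. Dilution is a consequence of one reading, not a certainty.

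A reader might infer that the model treats hospital-years as simply independent. It does not: the random hospital effect correlates all years of a hospital, and independence holds only given that effect.

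A reader might also infer that the effect is diluted and its standard error too small at once. The two belong to different codings. In simulation the allocated-arm coding had a mean standard error of about 0.50 against an empirical SD of 0.45 to 0.54, so it was not systematically understated.

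The wording about year within hospital could also mean a hospital-specific trend, which would absorb part of any drift. If so, the plan should say so. The phrase about the six-year baseline and study period could mean six years in total, which gives the mildest dilution, 12.5%.

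Finally, coding and degrees of freedom are often left to an analysis plan, which is not shown. That is fair for the degrees of freedom. But the article lists the terms of its primary model, and that list neither identifies the contrast nor includes a term for lasting change within a hospital.

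**Conclusion.** The point holds in a conditional form. As written, the primary model leaves open which contrast is tested. Under allocated-arm coding, a 25% effect shrinks to between 12.5% and 6.3%, depending on the number of baseline years, and change from baseline is not tested. Under switch-on coding the contrast is right, but type I error rises from 2.5% to about 5% to 12% if moderate correlation between years or lasting hospital shifts exist.

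Those correlations are assumptions; the documents give no figure for them. They are plausible over 6 to 12 years of data, but the documents do not support the stronger conclusion that the primary test is invalid. With no extra correlation, the switch-on model is sound. The figures also assume two-sided tests, equal weight for each year, and hospital-year means in place of individual episodes.

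**What to change.** - State the primary contrast as the between-arm difference in change from baseline, through an arm-by-period term or an explicit switch-on indicator. State which years count as baseline, and use the same years in the power calculation and the analysis.
- Add to the hospital and hospital-year effects either a random hospital-by-period effect or serial correlation across years within hospital.
- Test with a small-sample correction such as Kenward-Roger, so that the degrees of freedom reflect 24 hospitals (24 − 3 = 21 for a hospital-level comparison of change).
- Alternatively, model the post-intervention hospital rates with each hospital's own baseline rate as covariate, as the cost analysis already does.
- Carry the choice over to the secondary models that follow the same form.

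This changes analysis wording only and needs no new data. The cost is a somewhat wider interval; if the extra correlation proves absent, little is lost.
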